### Sample size

For sample size calculation, the higher the effect size and lower standard deviation in relation to the effect, the lower the sample size required to confirm the result. Thus, based on previous studies, the sample size was calculated using inspiratory muscle pressure as endpoint [18]. Considering a difference among treatments (effect size) of 15 cm H_2_O and a standard deviation (SD) of 12 cm H_2_O in the PI_max_, representing a 1.2 ratio (effect size/SD), using an α = 0.05 and power of 80%, nine patients would have to be included per group. In addition, considering a potential loss in patient follow-up of between 10% and 20%, the sample was set to 11 patients per group.

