#### QoL

QoL will be assessed using the Minnesota Living with Heart Failure Questionnaire [24]. Overall scores and the separate effects of physical and psychological perceptions of QoL will be analyzed.

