#### HRV analysis

Twenty-four-hour ECG recordings will be obtained with a SEER Light digital recorder (GE Medical Systems Information Technologies, Milwaukee, WI, USA). The recorded data will be analyzed using a MARS 8000 analyzer (Marquete Medical Systems, Milwaukee, WI, USA) [25, 26]. Briefly, time domain and frequency domain analyses of HRV will be performed according to the recommended by the European Society of Cardiology and North American Society of Pacing and Electrophysiology [27]. For time domain analysis, the following 24-h indices will be calculated: mean of all normal inter-beat (RR) intervals, standard deviation of all normal RR intervals, root mean square of successive differences of adjacent RR intervals, and rate of successive differences between normal adjacent RR intervals above 50 ms. For frequency domain analysis, the following spectral components will be calculated: low frequency (0.04–0.15 Hz), high frequency (0.15–0.5 Hz), and low-to-high frequency ratio. Spectral components will be expressed in absolute values (ms^2^ Hz) and in normalized units. Heart rate spectral analysis and time domain indices will be calculated using 5-min segments at rest during active breathing (*ujjayi*) and passive breathing (*pranàyama).*

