### Endpoints

The primary endpoints are inspiratory muscle strength by measuring maximal inspiratory pressure (PI_max_).

Secondary endpoints include (1) vagal activity in resting and exercising (HRV); (2) peak VO_2_; (3) QoL Minnesota scores as a specific inventory for patients with HF; (4) functional capacity (NYHA Classification); (5) volumetric ratios of left atrial and diastolic pressure gradients on echocardiography; and (6) changes in BNP/NT-proBNP tests between pre- and post-intervention measurements.

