### Statistical analysis

Initially, a descriptive analysis will be performed and data will be expressed as absolute and relative frequency, besides mean and standard deviation or quartiles, accordingly. The treatment groups will be compared using the generalized estimating equation, specific for repeated measurements, in order to compare the effects (means) across the three groups and the two times, in addition to the group × time interaction. The generalized estimating equation matrix of robust estimator covariance and exchangeable work correlation matrix will be used if normal distribution is found and will be analyzed by an identity binding function. In contrast, if an asymmetrical distribution is found, data will be analyzed using a gamma distribution linked to a logarithmic function. When significant, the factors under study will be compared by Bonferroni’s post-hoc test. Correlations will be described by the Pearson’s or Spearman’s test. The PASW18 (version 18.0, SPSS, Chicago, Illinois, USA) will be used in this analysis.

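### The observed distribution, by no stated criterion, decides whether the primary PImax contrast is a difference or a ratio, although the trial is sized on a difference in cm H2O

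*Protocol article*

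**What the plan says.** The Statistical analysis section of the protocol article plans a GEE to "compare the effects (means) across the three groups and the two times, in addition to the group × time interaction". It then sets two branches. The robust covariance with exchangeable correlation "will be used if normal distribution is found and will be analyzed by an identity binding function". Otherwise, "if an asymmetrical distribution is found, data will be analyzed using a gamma distribution linked to a logarithmic function".

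The section does not say how asymmetry is judged, or on what (pooled values, each group, each visit, residuals). The rule covers every outcome, including PImax, which the Endpoints section names as primary.

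The Sample size section works on the original scale: "Considering a difference among treatments (effect size) of 15 cm H_2_O", with an SD of 12 cm H2O.

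Among the heart rate variability measures, the HRV analysis section lists the "rate of successive differences between normal adjacent RR intervals above 50 ms". Heart rate variability is the first secondary endpoint.

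**The concern.** The choice of link is also a choice of effect measure. With the identity link, the group × time term is a difference between arms in mean change, in cm H2O. With the log link it is a ratio of ratios of means. A rule that picks between them from the observed distribution leaves the primary effect measure open until the data are in, and one of its two answers is not on the scale for which the trial was sized. If the branches can disagree on significance, the trial's conclusion depends partly on a preliminary check that the text does not define.

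A smaller concern is that the gamma branch is offered for every outcome, while the gamma distribution is defined only above zero.

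**Working it through.** **Inputs.** From the Sample size section: difference 15, SD 12, α = 0.05, power 80%, nine per group, set to 11 for losses of 10–20%. Assumed, because the document gives none: baseline PImax, pre–post correlation 0.5, and the SD of 12 read as the SD of levels at each visit.

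**1. The plan's own figure.** Normal approximation: n per group = 2(z_α + z_0.80)² / (δ/σ)².
- One-sided, with the printed ratio of 1.2: 2 × (1.645 + 0.842)² / 1.44 = 8.6, so 9.
- Two-sided: 2 × (1.960 + 0.842)² / 1.44 = 10.9, so 11. With 15/12 = 1.25 it is 10.05, also 11.
- Allowance for losses: 9/(1 − 0.18) = 10.98, so 11.

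Nine is thus reproduced on a one-sided test; the text does not state sidedness. What matters here is that δ is an absolute difference.

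**2. The two contrasts.** Let an arm's mean go from a to a + c.
- Identity link: difference between arms in c.
- Log link: ratio between arms of (a + c)/a.

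Equal gains of 15:
- Baselines 60 and 75: difference 15 − 15 = 0; ratio (75/60)/(90/75) = 1.25/1.20 = 1.042.
- Baselines 50 and 70: difference 0; ratio (65/50)/(85/70) = 1.071.

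The nulls coincide if baselines are equal or if no arm changes. The planned effect also has no single value on the log scale: +15 against no change is a ratio of 1.375 from a baseline of 40, 1.25 from 60, 1.19 from 80 and 1.15 from 100.

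**3. How often the branches disagree.** Simulated GEE, 11 per arm, SD 12, correlation 0.5, exchangeable correlation, robust SE, interaction tested at 5%, 400 runs:

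| Scenario | Identity significant | Gamma-log significant | Disagree |
|---|---|---|---|
| No effect, baselines 60 | 7.8% | 6.8% | 1% |
| +15 in both yoga arms, baselines 60 | 89% | 83% | 6% |
| +15 in every arm, baselines 75/60/60 | 7.8% | 15.8% | 13% |

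The simulation error on the 13% is about √(0.13 × 0.87/400) = 1.7 points. A second simulation with the same assumed SD, correlation and arm size gave disagreement of 0%, 6% (power 88% against 83%) and 9%. Both branches exceed 5% with no effect; that is separate from this point.

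**4. How likely the third scenario is.** With SD 12 and 11 per arm, the SE of a baseline difference is 12 × √(2/11) = 5.1. A gap of 15 is 2.9 SE, about 0.3% for a given pair. For the largest gap among three arms, simulation gives a median of 5.7, above 10 in 12% of trials and above 15 in 1%. If the baseline SD were 20 (assumed), these become 9.6, 47% and 18%.

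**5. The trigger.** If Shapiro–Wilk at 5% were used (assumed), truly normal data would be sent to the gamma branch in 6% of trials when all 66 values are pooled, about 10% if either visit (n = 33) counts, and 27% if any of the six group-by-visit cells counts. A true skewness of 0.7 at n = 33 would be detected only 27% of the time.

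**6. Zeros.** The gamma log-density at 0 (shape 2) is minus infinity, and the deviance term −log(y/μ) is infinite at y = 0. The RR index is zero whenever no successive difference exceeds 50 ms.

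**The case against.** Both branches and both links are stated in advance, and naming the test for asymmetry is ordinary content for an analysis plan that is not shown. The Study design section blinds the analysts to groups and outcomes. The nulls separate only if arms, controls included, share a non-zero change and baselines differ. Randomisation makes a 15-point gap rare at SD 12, and with no effect and equal baselines the models hardly ever disagree.

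Most of this stands and limits the size of the problem. Blinding answers any suggestion that the more favourable scale would be picked, and no such suggestion is made. It does not answer the main point: the text itself makes the effect measure depend on the data, and naming a test would not change that.

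A reader might also infer that the gamma branch would discard the patients who respond best. The document does not support this:
- It states no exclusion of zeros. How they would be handled is not said, and a GEE uses only the gamma mean–variance relation, so the consequence of a zero depends on handling and software.
- PImax is positive, and higher is better.
- The QoL section says that "Overall scores and the separate effects of physical and psychological perceptions of QoL will be analyzed", but gives no score range or direction.
- The Endpoints section lists "changes in BNP/NT-proBNP tests between pre- and post-intervention measurements", but the model compares levels at two times, so change is the interaction and the modelled levels are positive.
- For the RR index, listed under vagal activity, a zero is the lowest value and not a best response.

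**Conclusion.** The point holds as a modest defect in a stated rule. The scale of the primary group × time contrast is not fixed, and one of the two possible scales does not match the additive 15 cm H2O behind the sample size. Under the assumed inputs, the choice of branch alters the significance call in about 0–1% of trials with no effect, about 6% with the planned effect (power about 88% against 83%), and about 9–13% with a 15-point baseline gap and equal gains. The last case is uncommon at SD 12 and more likely if baselines vary more widely. A reader should not infer that the primary result would often reverse.

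The secondary point is narrower: the gamma distribution does not admit a zero, and at least the RR index can be zero by definition. No claim is made about which patients, if any, would be lost.

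**What to change.** In the Statistical analysis section:
- Prespecify for PImax the GEE with identity link and robust covariance, reported as a difference in mean change in cm H2O, whatever distribution is observed. With robust covariance this compares means without requiring normality.
- Use the same model for any outcome that can be zero.
- Reserve the log-link model for strictly positive outcomes named in advance, such as BNP or NT-proBNP levels.
- Optionally, add a bootstrap or permutation p-value as a sensitivity analysis for skewness.

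The cost is wording only, with no new data or patients. The downside is some loss of efficiency if PImax proves strongly skewed. The Trial status section reports 18 patients already through the trial, so the choice should be fixed and dated before outcome data are examined.

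### Bonferroni applied after a significant three-group test is more conservative than three arms require; a closed test would gain up to about 11 points of pairwise power, provided the tests hold their size

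*Protocol article*

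**What the plan says.** The Endpoints section of the protocol article makes PImax the primary endpoint. The Statistical analysis section compares means by GEE "across the three groups and the two times, in addition to the group × time interaction", with a robust covariance and an exchangeable working correlation. It then adds: "When significant, the factors under study will be compared by Bonferroni’s post-hoc test". Pairwise comparison is thus conditional on a significant model term and is Bonferroni-adjusted as well.

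The Sample size section plans on "a difference among treatments (effect size) of 15 cm H_2_O". It puts the SD of PImax at 12 cm H2O, the ratio of the two at 1.2, alpha at 5% (sidedness not given) and the target power at 80%. Its conclusion is that "nine patients would have to be included per group"; enrolment is then raised to 11 in each arm because 10% to 20% may be lost. It makes no allowance for several pairwise comparisons.

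**The concern.** The useful answers from this trial are pairwise: active against control, passive against control, and active against passive. Three arms give three pairwise null hypotheses, and any two of them together imply the third and hence the global null. Once the global null is rejected, the only hypotheses left are single pairwise nulls, and each can be tested at the full 5%. That is a closed test. It is special to three groups.

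Under those conditions, lowering each pairwise level to 0.05/3 gives more protection than a 5% family-wise target needs. In a trial of 33 patients the lost power can only be recovered through the analysis or through more patients.

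**Working it through.** **Inputs.** From Sample size: difference 15, SD 12, 9 evaluable and 11 enrolled per arm. Assumptions, because the article does not say: two-sided 5%, and SD 12 is the SD of the change in PImax.

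**The plan's own figure.** 15/12 = 1.25, stated as 1.2. With n = 2(z_α + z_β)²/ratio²:
- One-sided 5%, ratio 1.2: 2 × (1.645 + 0.842)²/1.44 = 8.6, so 9 per group.
- Two-sided 5%: 10.9 (ratio 1.2) or 10.05 (ratio 1.25), so 11 per group; an exact t-test at ratio 1.25 needs 12.
- Dropout: 9/0.90 = 10, 9/0.85 = 10.6 and 9/0.80 = 11.25, so 11 is a middle value.

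The stated 9 therefore reproduces for one comparison at one-sided 5%. An exact two-sided t-test with 9 per group has 70% power before any multiplicity correction.

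**Bonferroni power, analytically (three-arm pooled variance, no gate).** SE = 12√(2/n); noncentrality = 15/SE; df = 3n − 3; level 0.05/3.
- n = 9: SE 5.66, noncentrality 2.65, df 24, critical t 2.57, power 54%.
- n = 11: SE 5.12, noncentrality 2.93, df 30, critical t 2.54, power 65%.

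**Simulation (200,000 trials per setting; normal data, F-test gate at 5%, then pooled t-tests).** One 15 cm pair, with the third arm equal to one of the two:

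| Per arm | Gate + Bonferroni | Closed test | Gain (points) |
|---|---|---|---|
| 9 | 54.0% | 65.5% | 11.5 |
| 11 | 65.4% | 76.3% | 10.9 |

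In this setting two differences are true. The chance of finding both rises from 39% to 58% at 9 per arm and from 51% to 70% at 11. With Bonferroni in place the gate hardly matters: at 9 per arm power is 54.0% with it and 54.1% without it.

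**Graded effects 15/7.5/0.**
- Largest pair: 53.6% to 58.6% (n = 9) and 65.1% to 69.5% (n = 11), about 5 points.
- 7.5 cm pairs: about 12.6% to 23.0% (n = 9) and 15.9% to 28.1% (n = 11), about 10 to 12 points.

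**Family-wise error with these exact-size tests.** Closed: 5.0% under the global null and 4.9–5.1% when one arm differs. Gate plus Bonferroni: 4.2% and 1.7%.

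**Same comparison with uncorrected robust tests.** Sandwich-type Wald tests with chi-square and normal cut-offs, as an approximation to the planned GEE:

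| Per arm | Truth | Closed | Gate + Bonferroni |
|---|---|---|---|
| 9 | no difference | 11.0% | 9.5% |
| 9 | one arm differs by 15 | 8.2% | 3.9% |
| 11 | no difference | 9.7% | 8.3% |
| 11 | one arm differs by 15 | 7.6% | 3.4% |

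The power gain here is 8–9 points for a 15 cm pair, but from tests that exceed their nominal level.

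**Which gate.** The plan tests group, time and group × time. If only time has an effect and that opens the gate, unadjusted between-arm comparisons at the two visits have about 21% family-wise error (assumed within-patient correlation 0.5). The closed-test argument needs the 2-df test of the same between-arm contrasts as its gate.

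**The case against.** The strongest objection is that the adjustment is not redundant in the analysis as planned. A reader might infer from the closed-test argument that Bonferroni buys nothing here. The article does not support that: it specifies a GEE with robust covariance, and with 9 to 11 patients per arm the approximating simulation shows Bonferroni holding the error below 5% when one arm differs, where the closed test gives about 8%. Under the global null it does not cure the inflation (8–9% against 10–11%). This stands, and it makes a size-holding test a condition of the change.

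A reader might also take the reference to factors to mean Bonferroni over all six group-by-time cells: 15 pairs at 0.0033 each, and much lower power still. The sentence allows that reading but does not state it, so no figure for it is relied on. What can be said is that no pair of cells compares change between arms, because a difference in change involves four cells.

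Finally, Bonferroni is valid and supports simultaneous intervals, and detailed contrasts may sit in an analysis plan that is not shown. Both points are fair. The criticism is confined to what the article itself fixes: adjustment on top of a gate.

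**Conclusion.** The point holds as an efficiency improvement. With three arms and tests that hold their size, the planned rule is more conservative than 5% family-wise control requires. The cost is about 11 points of power for a 15 cm pair when the third arm equals one of the two, and under graded effects about 5 points for the largest pair and 10–12 for the smaller ones. These figures rest on the protocol's 15 and 12 cm H2O, on SD 12 being the SD of the change, and on two-sided 5%.

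It is not an error-rate fault. Nor should the result be read as a licence to drop Bonferroni and leave the rest of the plan unchanged: neither the present gate on any significant factor nor the uncorrected robust test is sufficient for that.

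**What to change.** For PImax:
1. Name three contrasts of change, or of the baseline-adjusted post value: active–control, passive–control, active–passive.
2. Gate them on the 2-df group × time test (or the ANCOVA group test) at 5%, and not on the group or time main effect.
3. If the gate is significant, test each contrast at 5% without further adjustment. Run no post-hoc tests over group-by-time cells.
4. Use a test that holds its size at 9–11 per arm: ANCOVA or a linear model on change with t and F reference distributions, or a GEE with a small-sample correction. Without this step, keep Bonferroni.

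The cost is a few sentences in the analysis section and possibly a change of model, with no extra patients or visits. The pairwise 95% intervals will not be simultaneous and should be labelled unadjusted. Trial status reports 20 enrolled and 18 completed, and Study design keeps the analysts blinded to groups and outcomes, so the change should be dated and documented before unblinding.

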## Discussion

Patients showing HFpEF have poor functional capacity despite preserved systolic function, and little has been added to the treatment of those patients. Recent research indicates that patients with restrictive ventilation, poor functional capacity, or peripheral abnormalities have more symptoms of exercise intolerance. Therapeutic strategies are necessary to improve exercise tolerance by targeting the integrated functions of these systems [29].

Traditionally, yoga is a complex physical practice associated with specific respiratory techniques [30]. Currently, it has been recommended in risk reduction programs [11] and cardiovascular rehabilitation [31], and its benefits include well-being, cognitive and motor improvement, positive effects in the treatment of hypertension [30], decreasing inflammatory process [32], and improved functional capacity of HFrEF patients [12]. In HFpEF patients, there are scarce reports based on the functional and neuromuscular properties during an acute or adaptive response to physical yoga and/or breathing practices.

This trial will assess the effects of yoga and specific breathing techniques as a non-pharmacological intervention in order to improve patients with HFpEF by promoting a decrease in the dyspnea degree during rest and exercise intolerance, which may represent a new treatment possibility for those patients. To this end, the NYHA classification will be assessed.

In order to reduce trial bias, this study has been carefully designed according to the PROBE concept [33], in which patients will be randomly allocated into intervention groups in a researcher-independent way, since the statistics department in the HCPA facility has a central phone for randomization. Furthermore, the performance bias will be controlled by single blinding according to researcher participation on trial.

Finally, all the results obtained in this trial will be published fulfilling all criteria of the CONSORT 2010 statement and its extension to non-pharmacological intervention.

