## Methods/design

### Study design

A PROBE (prospective randomized open blinded end-point) parallel-group trial with three groups will be conducted at two specialized HF clinics (HF Clinic at Hospital de Clínicas de Porto Alegre (HCPA), RS, Brazil, and the HF ambulatory at Hospital ULBRA-Mãe de Deus, Canoas, RS, Brazil). The researchers will be divided according to their specific role in this study as (1) interveners – those performing the protocol interventions (blinded for outcomes, but not for groups); (2) medical appraiser – responsible for performing clinical tests (blinded for groups, but not for outcomes); and (3) analysts – those responsible for the statistical analyses (blinded for both groups and outcomes). The individuals will be instructed to avoid talking with the research team about protocol intervention and clinical trials.

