### HF clinic and team approach

The two HF clinics participating in this trial are staffed by a multidisciplinary team of cardiologists, physical educators, physiotherapists, and nurses. On average, patients will start the protocols as soon as they conclude preclinical testing and will be randomized either to one of the intervention groups, or to the control group. In order to strengthen adherence to the study, the team will keep in touch by phone with the patients to reinforce their participation and confirm attendance at scheduled tests and interventions, or to understand the reasons for possible absences. Both centers have facilities that allow the performance of the yoga interventions described in the present study.

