#### Pulmonary function

Inspiratory muscle function testing will be performed using a pressure transducer (MVD-500 V.1.1 Microhard System, Globalmed, Porto Alegre, RS, Brazil) connected to a system with two unidirectional valves (DHD Inspiratory Muscle Trainer, Chicago, Illinois, USA). Maximal static inspiratory pressure will be determined in deep inspiration from residual volume against an occluded airway, with a minor air leak (2 mm). The highest pressure within six measurements will be used for analysis. The PI_max_ measurement will be performed at rest and at the 5th and 10th min after CPET. Predicted values will be corrected for age, sex, and weight [14]. Additionally, in order to determine the inspiratory muscle endurance, an incremental test will be used in which patients will breathe continuously through a mouthpiece connected to a measure device. The patients will use an initial load of 50% PI_max_, and increments of 10% PI_max_ will be added every 3 min until the patient is unable to continue breathing. The highest inspiratory pressure that the individual is able to sustain for at least 1 min (Pth_max_) will be considered as the measure for inspiratory muscle endurance and will be expressed as a rate of maximal inspiratory pressure (Pth_max_/PI_max_). In the second stage of the protocol, individuals will breathe against a constant inspiratory submaximal load equivalent to 80% Pth_max_, and the time elapsed to task failure will be defined as the inspiratory endurance time. The Powerbreathe K5 will be used for patients with IMW and for those with normal respiratory fraction, for age and sex [15, 16].

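### The Discussion credits single blinding with controlling performance bias, but the blinding described limits detection and analysis bias, and performance bias remains in each yoga-versus-control contrast

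*Protocol article*

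**What the plan says.** The Discussion of the protocol article, after naming the PROBE concept and central randomization, adds that "the performance bias will be controlled by single blinding according to researcher participation on trial".

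The Study design section sets out who is blinded to what:

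- The trial is "A PROBE (prospective randomized open blinded end-point) parallel-group trial with three groups".
- Interveners are "those performing the protocol interventions (blinded for outcomes, but not for groups").
- The medical appraiser is "responsible for performing clinical tests (blinded for groups, but not for outcomes").
- Analysts are "those responsible for the statistical analyses (blinded for both groups and outcomes").
- For participants there is one instruction: "The individuals will be instructed to avoid talking with the research team about protocol intervention and clinical trials". This protects the appraiser's blinding. It does not blind the participant.

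The three arms are described under Study protocol. Each yoga arm has sessions of about 45 min, 16 in all over 8 weeks, with a 7-min closing relaxation common to both. Controls continue their usual drugs and daily activities, do no structured exercise, and come back for testing at 8 weeks. No sham or attention sessions are described for them.

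The primary endpoint is PImax (Endpoints). Under Pulmonary function, "The highest pressure within six measurements will be used for analysis".

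**The concern.** Performance bias arises when patients, or the people treating them, know the allocation and behave differently because of it, through effort, attention, encouragement or other care. Only blinding of those people can remove it by blinding. Blinding the tester and the analyst deals with a different problem: how outcomes are measured and analysed.

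The Discussion sentence therefore credits the design with a property that the Study design section does not give it. This touches the main conclusion because the key outcomes depend partly on the patient:

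- PImax is the best of several maximal inspiratory manoeuvres that the patient performs.
- The exercise test that yields peak VO2 runs to volitional fatigue.
- The Minnesota score is a patient questionnaire.
- NYHA class rests largely on symptoms that the patient reports.

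Expectation and attention in the yoga arms would be likely to move these outcomes in the direction of the hypothesis. The section on independent variables names respiratory management with different rhythms as the main exposure. If the Discussion sentence stands, a yoga-versus-control difference invites attribution to the breathing technique alone, although the comparison also contains supervision, attention and expectation.

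**Working it through.** The plan gives no figure for this point, so there is none to reproduce. The check sets the sections side by side, followed by one piece of arithmetic on contact time.

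**1. Who knows the group**

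| Person | Knows the group? | Source | Bias that blinding this person would limit |
|---|---|---|---|
| Patient | Yes: open trial, no patient blinding described, and attending yoga sessions or none reveals the arm | Study design; Study protocol | Performance bias; bias in self-reported outcomes |
| Intervener | Yes, stated | Study design | Performance bias |
| Medical appraiser | No, stated | Study design | Detection bias |
| Analyst | No, stated | Study design | Analysis bias |

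The two rows through which performance bias acts are the two without blinding to group. The rows with blinding concern other biases.

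**2. Supervised contact by arm**

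Inputs: 16 sessions; about 45 min per session in either yoga arm; 7 min of relaxation (all from Study protocol).

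- Each yoga arm: 16 × 45 min = 720 min = 12 h.
- The text does not say whether the relaxation falls within the 45 min. If it is additional, it adds 16 × 7 = 112 min, about 1.9 h, for a total of about 13.9 h.
- Control: 0 sessions, 0 h.

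The planned difference in supervised contact is thus about 12 h (up to about 14 h) for active yoga versus control and for passive yoga versus control. Between the two yoga arms it is about 0 h.

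**3. What the blinded appraiser does and does not protect**

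An appraiser who does not know the group cannot coach one arm harder than another, so this route of bias in PImax and the exercise test is limited. The patient's own effort and expectation are not. That PImax depends on effort is inferred from the manoeuvre described under Pulmonary function; the article does not use that term.

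**4. Other safeguards in the text**

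The section on sociodemographic and clinical variables tells patients to keep their activities and diet stable and requires drug changes to be recorded. The section on independent variables requires effects to be controlled for concomitant exercise, co-intervention and treatment changes. These address the co-intervention route of performance bias. They do not address attention, expectation or effort at testing, and none of them is blinding.

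**The case against.** The strongest reply is that nothing is hidden. The article calls the trial open in the abstract and under Study design, states that interveners are not blinded to group, and names PROBE again just before the disputed sentence. Patients can hardly be blinded to yoga, and usual care is an ordinary comparator. Interveners are blinded to outcomes, so they cannot adapt delivery to test results, and the co-intervention rules close part of the remaining gap. All of this stands. The open design is not the fault. It does not rescue the sentence, which says that blinding controls performance bias, when blinding to group does not reach the people through whom that bias acts.

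Four stronger readings are tempting and are not supported:

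- **That every comparison on the primary endpoint is compromised.** The two yoga arms share session number, approximate length and closing relaxation, so their contrast is similar in contact. The appraiser's blinding also gives PImax some protection.
- **That the telephone calls favour the yoga arms.** The article says that "the team will keep in touch by phone with the patients to reinforce their participation and confirm attendance at scheduled tests and interventions", without limiting this by arm. Fewer calls to controls would be conjecture.
- **That the bias has a known size in cm H2O.** The documents give no effect of effort or attention on PImax, and hours of contact do not convert into one.
- **That natriuretic peptides or echocardiography could verify a PImax gain.** They do not measure inspiratory strength, and some patients have BNP while others have NT-proBNP. A null result there would not show that a PImax difference was bias.

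**Conclusion.** The Discussion sentence is wrong as written. Blinding of the appraiser and analysts limits detection and analysis bias. Performance bias is only partly addressed, by the stable-routine and co-intervention rules, and it remains in both yoga-versus-control contrasts, where planned supervised contact is about 12 h against none. The active-versus-passive contrast is much less affected.

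The conclusion rests on two inferences: that patients know their arm, which follows from an open trial of yoga sessions against no sessions, and that PImax, peak VO2, Minnesota score and NYHA class respond in part to a patient's effort or report. It does not depend on any assumed size of bias. A reader might infer that a positive yoga-versus-control result would be uninterpretable. The documents do not support that: the comparison remains a valid randomized estimate of the supervised programme as a whole. What it cannot do is isolate the breathing technique. The point deserves correction because it bears on the primary endpoint, but it is a matter of statement and interpretation, not of the design's validity.

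**What to change.** Replace the Discussion sentence with wording such as: *Blinded appraisers and analysts limit detection and analysis bias. Patients and interveners know the allocation, so performance bias in comparisons with control is not controlled by blinding; it is addressed only in part by the rules on stable routine and co-intervention.*

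Add a limit on the conclusion: yoga-versus-control differences in PImax, peak VO2, Minnesota score and NYHA class estimate the whole supervised programme, including attention and expectation, and not the breathing technique alone. Note that the active-versus-passive contrast has similar contact and is less exposed to this problem. Carry the same wording into the results report.

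No change to design, sample size or measurement is needed. A new coaching script for the PImax efforts is not advised now: Trial status reports 20 of the 33 expected patients enrolled and 18 completed, so a script would alter how the primary endpoint is measured partway through the trial, and for patients still in follow-up between their pre-test and post-test.

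The cost is a less favourable statement about bias and a narrower conclusion. Both changes can be made before results are known.
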